### Blinding

Due to the nature of the intervention, trial participants and treating physiotherapists are unable to be blinded. However, the assessors who are undertaking the outcome assessments will be blinded to participant allocations. The initial baseline assessment will be undertaken, following written informed consent obtained by the research therapist, prior to randomisation. Every effort will be made to ensure the two follow-up assessments (at 15 and 27 weeks post-randomisation) remain blinded. At each assessment time point, the assessor will be asked to record if they were un-blinded to group allocation, and if so, the reasons for this.

### Interventions

The BRiMS programme is delivered as a 13-week therapy-led personalised education and exercise intervention. It is structured to maximise the development of self-efficacy and support participant engagement. BRiMS aims to address modifiable fall risk factors such as poor balance and mobility and enable self-management by the use of individualised mobility, safety and falls risk management strategies.

The development of BRiMS has been informed by the MRC framework for the development and evaluation of complex interventions [26] through a comprehensive programme of research [9, 11, 32–34] and input from internationally recognised experts [23, 35].

BRiMS includes a strong focus on home-based activities, supported by online resources and three group sessions interspersed over the duration of the programme. The programme also includes two ‘one-to-one’ sessions (in weeks 1 and 2) to enable individualised assessment, goal planning and development of exercise plans. A home-based online work package overarches the programme, supporting both educational and exercise components and enabling participants to personalise the programme and apply the activities in their daily lives from the outset (www.brims.org.uk). Developing and supporting motivation is addressed throughout by using innovative functional imagery techniques [36] to supplement established motivational techniques.

Whilst the BRiMS programme is manualised, it is structured to enable tailoring of the components to meet the individual needs of participants (Fig. 2).

**Fig. 2 Fig2:**
[figure not shown]
BRiMS programme activities

The BRiMS education component aims to improve exercise self-efficacy and enhance the individual’s knowledge and skills about falls prevention and management [37]. This is delivered through a mix of home and group activities embedded throughout the course of the programme. It utilises group brainstorming, problem solving and action planning [38] and applies the principles of cognitive behavioural therapy (CBT). During group sessions, peer modelling, vicarious learning, social persuasion and guided mastery are used to boost self-efficacy [39]. Activities which encourage the setting and imagery of short-term exercise goals are employed to boost desire to achieve them, and images of failure are ‘rescripted’ [40].

The BRiMS exercise component supports the participant to undertake at least 120 min of gait, balance and functional training per week. It has been designed to be predominantly home-based, with exercise planning and progression undertaken in partnership between the participant and programme leader. The group sessions include exercise activities to encourage peer support and problem solving. Additionally, BRiMS integrates an online exercise prescription resource [41] to support and guide home-based practice (www.webbasedphysio.com).

### Usual care

This feasibility trial will use a usual clinical care control group. Whilst usual care varies across the country [42], in those with SPMS, physiotherapy input is generally provided when an event has caused a significant deterioration in the person’s ability to function (e.g. a respiratory infection or an injurious fall). The standard physiotherapy care pathway usually comprises short intermittent episodes of face-to-face intervention. Typically, presenting problems are managed (e.g. providing mobility aids, a written home exercise programme and advice) rather than focusing on the promotion of long-term self-management strategies. In this trial, the usual care received (including health/social care interventions and medications) will be recorded within the health economic assessment of resource utilisation. In this feasibility study, the therapists providing the intervention are not involved in providing the control group with ‘usual care’, thereby avoiding potential contamination.

### Data collection and outcome measurements

Participant data will be collected during face-to face visits and through the return of postal diaries (see Table 1 for details). All participants will attend for three trial assessment visits undertaken by the blinded research therapists at baseline, 15 weeks (±1 week) and 27 weeks (±1 week) after randomisation. These dates allow the delivery of the pre-scheduled BRiMS programme to be completed prior to the first follow-up assessment. Deviations from this schedule will be monitored and reported on a protocol deviation form.

**Table 1 Tab1:** Data collection and outcome measures

Outcome measure	Baseline		15 weeks post-randomisation (±1 week)	27 weeks post-randomisation (±1 week)
Demographics and history	x	Randomisation to intervention or control		
Provide falls diaries	x		Returned by post every 2 weeks	
EDSS	x			
MSWS-12vs2.0	x		x	x
MSIS-29vs2.0	x		x	x
EQ-5D-5L	x		x	x
Falls frequency	x		x	x
Activity monitoring	1 week		1 week	1 week
2-minute walk test	x		x	x
Mini-BEST	x		x	x
Functional Reach Test	x		x	x
Falls Efficacy Scale	x		x	x
Community Participation Indicators	x		x	x
Participant Resource Use questionnaire	x		x	x
Adverse events			x	x
Qualitative interviews				x

The following data will be collected during the trial:A.Feasibility outcomesData from screening, recruitment and follow-up logs will be used to generate realistic estimates of eligibility, recruitment, consent and follow-up rates.B.Clinical outcome measuresStandardised clinician-rated and patient self-reported clinical outcomes, which have demonstrated good reliability and validity in people with MS, will be measured. Further, in the main, these measures have been widely used in MS interventional studies, which will enable comparison between studies.Possible primary outcomes for the definitive trial
*Walking*—Multiple Sclerosis Walking Scale–12 item (MSWS-12) Version 2.0 [43].
*Health-related quality of life EuroQoL* (EQ-5D-5L) [44] and the 29-item *Multiple Sclerosis Impact Scale* (MSIS-29) Version 2.0 [45], which have been specified for use in health economic analyses in MS studies [46].Possible secondary outcomes for the definitive trial
*Falls frequency and injury rates*
Falls will be defined as “an unexpected event in which you come to rest on the floor or ground or lower level” [47]. In line with best practice guidance, the number of falls, injurious falls and associated use of medical services will be recorded prospectively using a patient-completed daily diary returned to the CTU in a FREEPOST envelope on a fortnightly basis [48].
*Activity level* using an activity monitor (activPAL™, Paltechnologies Ltd, Glasgow) [49].
*Walking capacity* using the two-minute walk test (fastest speed) (2MWT). This has been recommended as the standard objective walking test to be used in MS interventional studies [50].
*Balance* using the Mini-Balance Evaluation Systems Test (Mini-BEST) [51] and the Functional Reach Test (forwards and lateral) [52–54].
*Fear of falling* using the 16-item self-report Falls Efficacy Scale (International) (FESi) [55]. This has been recommended as the standard objective measure of fear of falling by the Prevention of Falls Network Europe [47].
*Community integration* using the self-report Community Participation Indicators (CPI) [56]. This has been recommended as an objective measure of participation for use in falls prevention studies by the International MS Falls Prevention Research Network [57].
C.Measures of adherenceAttendance at the five face-to-face sessions will be recorded; adherence will be calculated as a percentage. Engagement in the home-based programme (BRiMS online exercise package and educational packages) will be recorded based on the participants' web-based activity and participant reported information.This information, alongside the data obtained from qualitative interviews with participants (see E below) will be used to evaluate levels of adherence and to determine whether any amendments to the programme are required to improve engagement.D.Economic evaluationMethods for the collection of resource use, cost, and outcome data will be developed and tested in preparation for an economic evaluation alongside a full trial. Data on resource use associated with the setup and delivery of the BRiMS intervention will be collected via within trial reporting, including participant level contact and non-contact time for staffing input on delivery, equipment and consumable costs, training and supervision. Data on health and social care resource use will be collected at participant level using a Participant Resource Use (RU) questionnaire, developed for this trial [58]. The EQ-5D-5L will be used to estimate quality-adjusted life-years (QALYs), and is the expected primary economic endpoint (cost per QALY) in any future evaluation. The MSIS-8D [59, 60], an MS-specific preference-based (QALY) measure, will also be used, as this is expected to be of value in future sensitivity analyses.E.Process evaluationProcess evaluation is a key part of the intervention development process and will be guided by the MRC Process Evaluation of Complex Interventions Guidelines [61] and the National Institute of Health Behaviour Change Consortium framework [62].
Standardisation and fidelity of the interventionTwo research therapists (employed specifically for the trial) will undertake the blinded assessments using standardised written protocols. Treating therapists from each site will perform the interventions as part of their NHS physiotherapy role. For this feasibility trial, all treating therapists will undertake a training session as a group. They will receive a therapist manual that provides a clear structure to each session, details the session content and provides sample scripts. All treating physiotherapists have access to the programme website (containing comprehensive reference materials and a closed therapist discussion forum) to optimise fidelity to the intervention content and approach. Treatment fidelity of a random sample of a minimum of 25% of the delivered sessions will be assessed using audio recordings of the session. This sample will include at least two recordings of each session type (1:1 assessment, home visit and group sessions) and at least one session from each treating therapist. The assessment of fidelity will be undertaken by two members of the research team who are independent from the intervention delivery, using a checklist which has been informed by the Dreyfus System for Assessing Skill Acquisition [63] and an adaptation of the Motivational Interviewing Treatment Integrity scale [64]. Both reviewers will initially meet to discuss the fidelity assessment process and their expectations for each element of the checklist. They will then independently rate the same recording and compare and moderate their assessments prior to undertaking further reviews. Any uncertainties in further reviews will be resolved through discussion.
*Safety monitoring*
Throughout the trial, all possible precautions will be taken to ensure participant safety and wellbeing. Participants will be monitored for adverse events and serious adverse events (defined according to the Medicines for Human Use (Clinical Trials) Regulations, 2004) [65] via completion of their daily diaries and during follow-up assessments. Participants will be asked to report all adverse events in their diaries, whether they are thought to be related to the intervention or not. Diaries will be reviewed on receipt for reports of adverse events and responded to according to pre-defined adverse event and serious adverse event reporting procedures.
*Retention rates and withdrawals*
Each participant has the right to voluntarily withdraw from the trial at any time, without repercussions. This is distinct from participants in the intervention group terminating their involvement in the BRiMS programme.Discontinuation of the interventionParticipants in the intervention group may choose to discontinue the BRiMS programme, or may do so on the recommendation of a health professional, for example following an adverse event. Where appropriate, such participants will be asked to continue to attend blinded assessments as per protocol if this is feasible.Withdrawal from the trialAny participant may at any time after they have consented decide that they no longer wish to be part of the trial. This may be through personal choice (i.e. they withdraw their consent) or in consultation with a health professional, for example where it becomes impossible to provide outcome data or comply with any other trial procedures for whatever reason. In addition, a participant may be withdrawn following a significant protocol deviation, such as being randomised in error. In this event, the decision as to whether they should be removed from the trial completely or retained on an intention to treat (ITT) basis will be made through an independent adjudication by the Trial Steering Committee (TSC) who are blinded to group allocation [68].
Qualitative evaluationThe qualitative evaluation aims to:Assess the acceptability of the trial methods (both trial arms)Evaluate the acceptability of the intervention and identify possible adaptationsIdentify the components of the intervention perceived to be effective.

One-to-one telephone interviews with trial participants and a telephone focus group [66] with treating therapists will be undertaken by the regional BRiMS trial coordinators at the completion of the programme. A purposive sample of 10 participants will include people from different regions, different BRiMS intervention groups and a sample of control arm participants. Participants will be contacted and a mutually convenient time agreed to undertake a telephone interview within 2 weeks of the completion of their final trial visit. All treating therapists will be invited to participate in the telephone focus group which will be convened within 1 month of the completion of the final BRiMS programme delivery. All interviews will be digitally recorded and transcribed verbatim. The researchers will employ a reflexive approach throughout, utilising research diaries, field notes and critical reflection [67].

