### Randomisation and allocation concealment

The inclusion of group-based elements as part of the intervention necessitates the confirmed participation of a sufficient number of participants within a recruiting site before randomisation occurs. There are four sites where the intervention will be delivered. Once recruited, participants will ideally be randomised in blocks of 10, but the process can accommodate some flexibility within the limits 8–12 participants in each block. Randomisation will be undertaken when a sufficient number of individuals from a recruiting site have consented, indicated that they are able to attend the same BRiMS group (location, timing, should they be randomised to receive it), and complete baseline data have been collected. The decision to declare a block complete will be made by the research therapist in collaboration with the Trial Co-ordinator, Chief Investigator and local UK Clinical Research Collaboration registered Clinical Trials Unit (CTU) (Registration number 31). Randomisation will be undertaken a minimum of 3 and a maximum of 7 days prior to the commencement of the BRiMS programme delivery (for each block).

When the block size from a recruiting site consists of 8–12 participants, the participants will be randomised to the intervention or control group, using block simultaneous randomisation. The randomisation will be 1:1 when the block consists of an even number of participants, and when the block consists of an odd number of participants, the allocation ratio will be in favour of the intervention group in order to maximise recruitment potential and learning opportunities in this feasibility trial. Participants in a block will be numbered in the order in which they were first entered onto the trial website. The randomisation process will follow a strict and auditable protocol. Randomisation will take place after completion of all baseline assessments by the CTU Trial Manager via a secure web-based system. The randomised allocations will be computer-generated by the CTU in conjunction with an independent statistician, in accordance with the CTU’s standard operating procedure. The randomisation list and the programme that generated it will be stored in a secure network location within the CTU, accessible only to those responsible for provision of the randomisation system.

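### At the 25% minimum, the fidelity sampling rule does not ensure that group-session delivery is observed at every site or for each of the three group sessions

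*Protocol article*

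**What the plan says.** The rule is in the protocol article, section Data collection and outcome measurements, part E (Process evaluation), under standardisation and fidelity of the intervention.

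- Sampling fraction and method: "Treatment fidelity of a random sample of a minimum of 25% of the delivered sessions will be assessed using audio recordings of the session".
- Floor by session type: "This sample will include at least two recordings of each session type (1:1 assessment, home visit and group sessions".
- Floor by therapist: "at least one session from each treating therapist".
- Who delivers: "Treating therapists from each site will perform the interventions as part of their NHS physiotherapy role". The number of therapists per site is not given.

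The Randomisation section states that "There are four sites where the intervention will be delivered". The Interventions section describes "three group sessions interspersed over the duration of the programme" and two one-to-one sessions per participant. It also says what the group sessions are for: "During group sessions, peer modelling, vicarious learning, social persuasion and guided mastery are used to boost self-efficacy".

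The rule has no stratum for site or BRiMS group, and it treats the three group sessions as a single type.

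**The concern.** One-to-one sessions are counted per participant and group sessions per group, so a draw from all delivered sessions is mostly one-to-one. The floors do little to correct this. Two group recordings satisfy the type floor but cannot cover four sites. A one-to-one recording satisfies the therapist floor.

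The group sessions carry content that a one-to-one recording does not show, and leading a group is a different task from an individual assessment. If the group element is delivered poorly at one site, or if one of the three group sessions does not work as the manual intends, the recordings may contain no direct observation of it. The weakness could then pass into the definitive multi-centre trial, which this study is meant to prepare.

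**Working it through.** The article gives no number of recordings and no coverage probability, so there is no figure of its own to reproduce.

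**Inputs from the article**
- 60 participants, 40 in the South West and 20 in Ayrshire (Sample size).
- Blocks of ideally 10, range 8–12; 1:1 allocation in even blocks; four delivery sites (Randomisation).
- Three group sessions per programme and two one-to-one sessions per participant (Interventions).
- At least 25% sampled, at least two recordings per type, at least one per therapist (fidelity text).

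**Assumptions not in the article**
- Six blocks, split over the sites as 2/2/1/1 or 3/1/1/1. Both can be made to fit the 40/20 regional split.
- All planned sessions are delivered and recorded.
- The home visit is one of the two one-to-one sessions.
- One therapist per site.

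**Session counts**
- Intervention participants: 6 × 5 = 30.
- One-to-one sessions: 30 × 2 = 60. Group sessions: 6 × 3 = 18. Total 78.
- Sample: 0.25 × 78 = 19.5, rounded up to 20.
- Expected group recordings: 20 × 18/78 = 4.6, or about 4.7 among draws that meet the floors. About 15 recordings are one-to-one.

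**Chance that some site has no group recording, before the floors**

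For a set of sites with m group sessions between them, P(none sampled) = C(78−m, 20)/C(78, 20). This gives 0.4056 for m = 3, 0.1576 for m = 6, 0.0584 for m = 9, 0.0205 for m = 12, 0.0068 for m = 15 and 0.0021 for m = 18.

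With blocks 2/2/1/1 the sites hold 6, 6, 3 and 3 group sessions. By inclusion–exclusion:
- single sites: 2(0.1576) + 2(0.4056) = 1.1264
- pairs: 0.0205 + 4(0.0584) + 0.1576 = 0.4117
- triples: 2(0.0068) + 2(0.0205) = 0.0547
- all four: 0.0021
- P = 1.1264 − 0.4117 + 0.0547 − 0.0021 = 0.767

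With 3/1/1/1 the same sum gives 0.818.

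**With the floors imposed** (simulation, keeping only draws that meet both floors)

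| Blocks per site | Some site without a group recording | One of the three group sessions never sampled |
|---|---|---|
| 2/2/1/1 | 0.76 | 0.40 |
| 3/1/1/1 | 0.80 | 0.40 |

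**Sensitivity of the first column**
- Other layouts (five to eight blocks of 8–12), drawing from all sessions: 0.54 for eight blocks of 8 at two per site, up to 0.85 for five blocks of 12. Drawing 25% within the group type gives 0.51 and 0.88 for these two layouts.
- Base layouts, 25% drawn within the group type (5 of 18): 0.735 and 0.801.
- Larger overall fraction, 2/2/1/1, before the floors: 0.65 at 30%, 0.41 at 40%, 0.25 at 50%.
- Two therapists at each two-block site: 0.76, unchanged.

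A site with no recording of any type would arise in about 2.9% of unconstrained draws, and the therapist floor excludes it.

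**The case against.** A reader might infer that the sample cannot show how delivery differs between sites, or that a whole site may go unobserved. The article does not support either reading. Therapists come from each site and each must be recorded at least once, so every site is in the sample, and about 15 one-to-one recordings are spread across the sites. Comparing sites is also not a stated aim of the fidelity assessment. For fidelity of the programme overall, a random sample with type and therapist floors is a legitimate design, and nothing in the text contradicts itself.

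The bare floor of two group recordings should not be taken as the likely outcome either. Under the base assumptions exactly two occur in about 7% of draws, and two from the same site in about 2%. On average 2.8 to 2.9 of the four sites have a group recording, and the commonest result is one site missed (about 45% to 47%).

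There are other routes to noticing a failing group element: session attendance, the therapist focus group, and interviews sampled purposively across regions and BRiMS groups. The 25% is also a minimum, and the full protocol may spread the recordings further.

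These points narrow the concern but do not remove it. The other sources are reports of delivery or counts of attendance, not rated observation. The article states the sampling rule in full, and as stated it leaves coverage of the group component to chance. A modestly larger fraction does not repair that.

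**Conclusion.** The point holds as a limit of the design and not as an error. At the 25% minimum the rule does not secure observation of group-session delivery at each site or for each of the three group sessions. In the base case at least one site lacks a group recording in about 75% to 80% of draws, and one of the three sessions is missed in about 40%.

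The first figure rests on the assumed split of blocks over sites and moves between roughly 50% and 88% over the other layouts and ways of drawing examined. It stays above one half in every 25% layout tried, and falls if more than the minimum is sampled. What may be missing is group-session fidelity at one or more sites; delivery at every site is still seen in some form. The change is worth making because the same number of recordings can give better coverage.

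**What to change.** Keep the 25% total and stratify the random draw:

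- Select at random at least one group session from each BRiMS group delivered (about 6 of the 20), or at the very least one per site (4 of the 20).
- Constrain the selection so that each of the three group sessions is sampled at least once.
- Draw the remaining 14 or so from one-to-one sessions (assessments and home visits), stratified by therapist.

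The chance of a site without a group recording, or of a group session never assessed, is then zero by construction, provided the sessions are delivered and recorded.

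The cost is a sentence or two in the fidelity text, with the same number of recordings and the same two reviewers. Group sessions become slightly over-represented (6/20 = 30% of the sample against 18/78 = 23% of sessions), so fidelity should be reported by session type, or any overall score weighted back to the delivered mix. The change secures coverage of the group component. It does not provide a formal comparison between sites, since a site with one group may have a single group recording and different sites may be seen on different session content.
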